### Dental Examination Protocol at the 5-Year-Old Study Visit

#### VE Protocol

VEs occurred with participants in a semisupine position on an adjustable examination bed. The examiner stood to the side of, or behind, the participant. A portable LED light (220 lumens NÄVLINGE clamp spotlight IKEA) and a dental mirror were used and positioned to provide maximum illumination and visibility of the oral cavity without magnification. Cotton rolls and swabs were used to dry teeth and remove plaque. Compressed air was not used. Universal infection control standards and additional COVID-19 precautions were adhered to for all examinations.

Dental examinations were conducted by trained and calibrated registered dental practitioners (BJ and [name]) with experience and prior training in using the ICDAS index in research settings. Examiner BJ is an oral health therapist with 13 years of clinical experience, and examiner [name] is an oral health therapist with 5 years of clinical experience. Before commencing VEs, both examiners had participated in the web-based ICDAS and International Caries Classification and Management System (ICCMS) e-learning modules [26]. Additionally, a senior researcher and pediatric dentist (MS) with experience in conducting surveys using ICDAS and enamel defect indices facilitated a presentation on ICDAS using the ICDAS or ICCMS examiner training materials and training materials for the use of a modified molar incisor hypomineralization (MIH) index to assess for enamel defects (with permission from the author) [27]. A 2-hour calibration session on the application and interpretation of the indices, followed by a computer-based calibration exercise, took place. The computer-based calibration exercises were repeated until both examiners reached an intra- and interexaminer agreement of κ_w_>0.8.

Dental caries experience was recorded for each tooth surface using the 2-digit ICDAS criteria [28]. Code 01 could not be scored for smooth surfaces due to a lack of compressed air. Enamel defects were recorded using a modified MIH index describing each surface’s clinical presentation and the extent of the defect [29]. All tooth surfaces were examined using a systematic approach. The score given was the most severe of the 2 clinical presentations if multiple lesions were present on the same tooth’s surface.

All dental examination data were collected and managed using Research Electronic Data Capture (REDCap; Vanderbilt University) tool hosted at Murdoch Children’s Research Institute [30,31]. REDCap is a secure, web-based software platform designed to support data capture for research studies.

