### Dental Examination Protocol for 3D Models Obtained From an IOS

#### On-Screen Assessment

3D models will be examined in postprocessed formats on a laptop with a 15-inch monitor (Alienware, DELL). On-screen assessment in approximate natural colors and featuring fluorescence will occur using a noncommercial software (developed by 3Shape) that allows for visualization of the 3D models similar to the commercially available TPM software but permits faster examination of multiple models, making the viewing process more efficient for this study. 3D models will be viewed in rooms with natural lighting following a standard operating procedure. Examination periods will be at most 3 hours without breaks, and each 3D model will be viewed for less than 15 minutes to avoid examiner fatigue. The viewing time for each scan will be recorded.

Each model will be viewed first with color and then without color to inspect tissue geometry and possible surface cavitation. Dental caries experience for on-screen assessment of 3D models in color will be recorded using a merged ICDAS index. Codes 01 and 02 will be combined as “initial caries” because the 3D models cannot be dried, and codes 05 and 06 will be combined as “extensive caries” as discriminating between these latter categories is not of interest for this study (Table 1). These merged ICDAS categories still provide sufficient information about caries depth to support clinical decision-making [8,9,34].

**Table 1 table1:** Caries classification criteria for on-screen assessment of 3D models obtained with TRIOS intraoral scanners.

Caries extent	Merged ICDAS index: on-screen assessment—color		Merged modified ICDAS index: on-screen assessment—fluorescence	
Sound (ICDAS 0)	Sound tooth surfaces which show no evidence of visible caries	[figure not shown]	Sound surfaces (yellow-green fluorescence) with no visible fluorescence change (no red fluorescence)	[figure not shown]

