Initial (ICDAS 1-2)	First or distinct visual changes in enamel seen as carious opacity or visible discoloration (white spot lesion and brown carious discoloration) not consistent with clinical appearance of sound enamel and which show no evidence of surface break down or underlying dentine shadowing	[figure not shown]	First or distinct visual changes in enamel seen with orange-red fluorescence and altered green fluorescence not consistent with the appearance of sound enamel and which show no evidence of surface breakdown or underlying red fluorescence from dentine	[figure not shown]
Moderate (ICDAS 3)	A white or brown spot lesion with localized microcavitation of enamel without visible dentine exposure	[figure not shown]	Lesion with localized enamel breakdown with a distinct fluorescence change (usually intense red and reduced green), without visible dentine exposure. Usually, poorly delineated fluorescence change is seen	[figure not shown]
Moderate (ICDAS 4)	Obviously discolored dentine or dark shadow visible through apparently intact or microcavitated enamel, which has originated on the surface being evaluated	[figure not shown]	Lesion with or without enamel breakdown and poorly delineated distinct fluorescence change (intense red fluorescence and significantly reduced green fluorescence which appears almost black), deriving from dentine	[figure not shown]
Extensive (ICDAS 5-6)	A distinct cavity in opaque or discolored enamel with visible dentine	[figure not shown]	Distinct cavity with visible fluorescence changes and exposed dentine	[figure not shown]

3D models will then be viewed with the addition of fluorescence texture and dental caries will be recorded using a merged ICDAS index previously described by Ferreira Zandoná et al [35], where each scoring criteria has been modified to incorporate fluorescence features (Table 1). This index enables a consistent approach to classifying carious lesions using fluorescence and has been previously validated for the on-screen assessment of 3D models [19]. If multiple lesions are present on the same tooth’s surface, the caries classification will be the more severe of the 2 clinical presentations, per VE protocol. Data will be recorded using REDCap.

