### Outcome Measures

For agreement analyses, ICDAS and modified ICDAS codes will be collapsed for each surface into four categories labeled sound surface (0), initial caries (1), moderate (2), and extensive caries (3). A binary dental caries variable will be created for each surface, and the detection threshold will be initial caries (0 vs 1, 2, and 3).

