### Statistical Analysis

Data checking and cleaning will take place before analysis. Descriptive statistics for patient characteristics such as age, sex, caries prevalence, and the proportion of children with enamel defects will be reported. The total number of tooth sites included in the analysis will be reported.

Descriptive characteristics for the rater population will be reported, including qualification, clinical background, years of experience, and training results for each rater. Interrater and intrarater reliability for on-screen assessment of 3D models based on color and fluorescence using the intraclass correlation coefficient will be reported for all examiners. These estimates will be obtained from a multilevel model fitted to the surface-level data, accounting clustering (see below), and zero inflation.

To assess agreement among methods, we will undertake both surface-level and individual-level analyses. At the surface level, caries data naturally have 3 levels with surfaces clustered within a tooth, which are clustered within an individual. Therefore, for this analysis, we will use multilevel logistic regression to estimate method agreement while accounting for clustering for the tooth. Specifically, separate multilevel models will be fitted to compare VE with each of the alternative methods by including the variable method (VE vs on-screen assessment of 3D models in approximate natural colors, on-screen assessment of 3D models in approximate natural colors featuring fluorescence, and automated system) as the fixed effect. The coefficient estimates for the variable method will be used to indicate the level of agreement. The multilevel model will be fitted with a zero-inflated binomial distribution.

At the individual level, a numerical variable representing the number of lesions per individual will be generated and analyzed with 2 approaches. First, Bland-Altman method agreement analysis will be performed using a regression approach. Specifically, a model will be constructed to regress the difference between each pair of methods on their average [36]. The analysis will be repeated for each possible pair of methods. Second, for each possible pair of methods, an intraclass correlation coefficient will be estimated from a multilevel model fitted to the paired data consisting of the 2 measures for each individual obtained from the 2 methods, fitted with a zero-inflated Poisson distribution.

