A sensitivity analysis will explore the impact of the diagnostic threshold used on agreement estimates. Analyses will be repeated with the caries data dichotomized at alternative thresholds: the moderate and extensive thresholds. In the analysis of the moderate threshold, sound and initial surfaces will be labeled caries absent (0) and all remaining categories (moderate-extensive) will be labeled caries present (1). In the analysis of the extensive threshold, sound, initial, and moderate caries will be combined and labeled as caries absent (0) and only teeth with extensive caries will be marked as caries present (1). To evaluate if the surface location and presence of enamel defects impact the diagnostic agreement estimates, these variables will be included as additional variables in the regression models for the surface-level analyses, including interaction terms with the method. The surface location variable will have 3 levels for each visible tooth surface (occlusal, smooth, and proximal). Enamel defects will be a binary variable, defined as present or absent per person. The sensitivity analysis to compare the agreement between on-screen assessment of 3D models in approximate natural colors and on-screen assessment of 3D models in approximate natural colors featuring fluorescence will include additional variables, rater and timing, as fixed effects.

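### At the initial-caries threshold, VE and on-screen scoring apply different definitions on smooth surfaces, and the pooled coefficient and per-child counts do not separate them from the matched occlusal surfaces

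*Protocol article*

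**What the plan says.** All places are in the protocol article.

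- **VE Protocol.** Drying was by simple means: "Cotton rolls and swabs were used to dry teeth and remove plaque. Compressed air was not used". The consequence for scoring is stated for one surface type: "Code 01 could not be scored for smooth surfaces due to a lack of compressed air". No such limit is stated for occlusal surfaces.
- **On-Screen Assessment and Table 1.** Codes 01 and 02 are merged into one category when on-screen scores are recorded, "because the 3D models cannot be dried". The initial category (ICDAS 1-2) reads, for colour, "First or distinct visual changes in enamel seen as carious opacity or visible discoloration", and for fluorescence, "First or distinct visual changes in enamel seen with orange-red fluorescence and altered green fluorescence". Neither index makes an exception for smooth surfaces.
- **Outcome Measures.** One binary variable is made for every surface, and "the detection threshold will be initial caries (0 vs 1, 2, and 3".
- **Statistical Analysis.** One surface-level model is fitted for each comparison with VE, and "The coefficient estimates for the variable method will be used to indicate the level of agreement". The Bland-Altman and intraclass correlation analyses use the number of lesions per child, with no split by surface type. Surface location enters later, among the sensitivity analyses of the surface-level models, as an interaction with method. Its stated purpose is "To evaluate if the surface location and presence of enamel defects impact the diagnostic agreement estimates".
- **Discussion.** The limitations do not mention the code 01 restriction.

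**The concern.** The label *initial caries* does not mean the same thing for the two methods on smooth surfaces. A smooth surface showing only a first change must be recorded as sound by VE, whatever the examiner saw, but is to be recorded as initial caries on screen if the reader sees it. On occlusal surfaces both rules admit code 01.

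The estimates meant to show agreement at this threshold combine the two situations. If on-screen readers call any code 01 change on smooth surfaces, the method coefficient moves away from no difference and the per-child difference moves away from zero. A reader could not tell how much of that reflects the methods and how much the recording rule. Early detection is the stated motive of the study, and the Discussion says the results will inform whether 3D models can be used interchangeably with VE. The threshold concerned is the one at which that question matters most.

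**Working it through.** The article gives no agreement figure, prevalence or sample-size calculation for this point, so there is nothing to reproduce. The check has two steps.

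**Step 1: definitions side by side at the initial threshold**

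| Surface | VE positive | On-screen positive (colour or fluorescence) | Match as written? |
|---|---|---|---|
| Occlusal | code 01 or worse | code 01 or worse | yes |
| Smooth | code 02 or worse | code 01 or worse | no |
| Proximal | not stated whether the limit applied | code 01 or worse | unclear |

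At the moderate and extensive thresholds, codes 0, 1 and 2 all count as absent for both methods, so the mismatch vanishes. The automated system is applied to primary molar occlusal surfaces only, so its comparison with VE is outside the mismatch.

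The on-screen data cannot be re-cut later at code 02 or worse, because codes 01 and 02 are merged at recording.

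**Step 2: possible size, on assumed inputs**

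Assumptions, none of them from the article:
- 88 surfaces in a full primary dentition, 8 of them occlusal and 80 smooth or proximal, with the code 01 limit applying to all 80
- VE-positive prevalence of 5% on those 80 and 15% on occlusal surfaces
- a further 1%, 2% or 3% of the 80 with code 01 change that is called on screen
- perfect agreement otherwise

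The smooth-surface odds ratio is [p1/(1 − p1)] / [0.05/0.95], with p1 = 0.06, 0.07 or 0.08.

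For the pooled odds ratio, VE positives per child are 80 × 0.05 + 8 × 0.15 = 5.2, so the VE odds are 5.2/82.8 = 0.0628. On-screen positives are 5.2 + 0.8, 1.6 or 2.4.

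| Extra code 01 calls | Smooth OR | Pooled OR | Extra lesions per child |
|---|---|---|---|
| 1% | 1.21 | (6.0/82.0)/0.0628 = 1.17 | 0.8 |
| 2% | 1.43 | (6.8/81.2)/0.0628 = 1.33 | 1.6 |
| 3% | 1.65 | (7.6/80.4)/0.0628 = 1.51 | 2.4 |

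The occlusal odds ratio is 1.00 throughout.

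The assumptions were then widened: code 02 or worse on 3-10% of smooth surfaces, code 01 only on 1-5%, an occlusal share of 8-20% with 15% prevalence, and between none and all of the code 01 lesions called on screen. The pooled odds ratio then runs from 1.00 to 2.27, the smooth-surface odds ratio from 1.00 to 2.81, and the extra lesions per child from 0 to about 4.0. A middle case (occlusal share 8%, code 02 or worse 5%, code 01 only 3%, half of these called) gives a pooled odds ratio of 1.26, a smooth-surface odds ratio of 1.32 and about 1.2 extra lesions per child.

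These are marginal odds ratios. They indicate direction and rough scale, not the value the planned multilevel zero-inflated model would return.

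**The case against.** **The same physical limit may bind both methods.** For scanning, the Intraoral Scanning section mentions only gauze or cotton rolls for drying. A change that needs compressed air to be seen may therefore be absent from the colour model too. This stands: in colour the effect may be nil. A reader might infer that an excess of on-screen positives is to be expected even when the methods see the same things, and the article does not support that. What remains is that the on-screen rule admits code 01 on smooth surfaces and the VE rule does not.

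**With fluorescence, extra positives may be what the study wants to find.** VE is expressly not a gold standard here, and the aim is agreement with VE as performed. This is fair, and it rules out calling such positives over-detection. But the pooled coefficient cannot separate real additional detection from a category that VE was unable to record, so separate reporting helps under either reading.

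**The plan already looks at surface type.** Smooth versus occlusal is part of the third objective, and the location-by-method interaction can yield the surface-specific estimates. This stands for the surface-level models. It does not reach the lesion counts, it is placed as a sensitivity analysis, and it is not tied to the code 01 limit. An interaction could therefore be reported as a finding about surface location.

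**The figures rest on assumptions.** This stands. In addition, 80 of 88 is an upper bound, because surfaces must be visible on the model and proximal surfaces may not be affected. A reader might take 1.21, 1.43 and 1.65 as the distortion of the pooled estimate; they are smooth-surface values.

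**Conclusion.** The mismatch in the scoring rules is certain from the text; its effect on the results is not. It concerns VE versus on-screen comparisons at the initial threshold, in the pooled method coefficient and in the per-child counts. Under the assumptions above the pooled odds ratio could lie anywhere from 1.00 to 2.27 with otherwise perfect agreement. The lower end is plausible in colour. Larger values are more plausible with fluorescence, which the article's background describes as suited to early lesions. The comparison of colour with fluorescence is also untouched, since both use the same merged category.

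A reader might go further and conclude that the occlusal estimate should replace the all-surface result as the headline. The article does not support that. The first objective covers visible tooth surfaces generally, and a main result resting on about 8 of 88 surfaces (about 9%) would set aside most of what that objective addresses. The defect lies in how the initial-threshold results are to be presented and qualified, and it can be put right without new scoring.

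**What to change.** At the initial threshold, for VE versus each on-screen method:

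1. Report the estimates by surface type, taken from the interaction already planned, alongside the pooled estimate as main output. Keep the all-surface result in place.
2. Label the smooth-surface result *VE code ≥2 versus on-screen code ≥1*, so that any difference is read with the rule in view.
3. Split the per-child lesion counts into occlusal and non-occlusal for the Bland-Altman and intraclass correlation analyses.
4. State whether the code 01 limit also applied to proximal surfaces, which the analysis treats as a separate level.
5. Add the mismatch to the limitations, noting that merged on-screen codes prevent a common code 02 threshold on smooth surfaces.

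The cost is a little more output and lower precision in the occlusal stratum. No rescoring or new data are needed.

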#### Intraoral Scanning

Immediately following the VE, intraoral scanning took place using the TRIOS 4 scanner. This generation scanner has a high accuracy and fast acquisition time relative to other scanners on the market for complete arch scanning [32]. It also has specialized fluorescence technology built into its hardware which exposes teeth to 415-nm light during scanning. Light emitted from the teeth passes through a filter in the scanner (which filters out blue light) to be received by the scanner sensor. The fluorescence signal overlays onto the 3D models as green fluorescence and red fluorescence texture, aided by commercial software (TPM; version 2.3, Dental Desktop and TRIOS; 3Shape TRIOS A/S).

The clinical examiners were trained to use the 3Shape TRIOS software interface and intraoral scanning protocols. Before scanning, the dental lamp was switched off, and the window blinds were closed to limit external light during the scanning process as per manufacturer instructions [33]. Teeth were dried with gauze or cotton rolls, and the manufacturer-recommended scanning strategy was followed. The scanning procedure was considered adequate when the software had obtained sufficient information about tooth color and fluorescence for the region of interest. If the scan was incomplete, the reasons why the scanning procedure was inadequate were documented. The reasons for insufficient scan data included the scanner tip being too big to accommodate, gag reflex, and behavioral or developmental issues that limited cooperation with the scanning procedure. Both complete and incomplete 3D models were saved with the participant's unique identifier in the dental desktop software.

### Dental Examination Protocol for 3D Models Obtained From an IOS

#### On-Screen Assessment

3D models will be examined in postprocessed formats on a laptop with a 15-inch monitor (Alienware, DELL). On-screen assessment in approximate natural colors and featuring fluorescence will occur using a noncommercial software (developed by 3Shape) that allows for visualization of the 3D models similar to the commercially available TPM software but permits faster examination of multiple models, making the viewing process more efficient for this study. 3D models will be viewed in rooms with natural lighting following a standard operating procedure. Examination periods will be at most 3 hours without breaks, and each 3D model will be viewed for less than 15 minutes to avoid examiner fatigue. The viewing time for each scan will be recorded.

Each model will be viewed first with color and then without color to inspect tissue geometry and possible surface cavitation. Dental caries experience for on-screen assessment of 3D models in color will be recorded using a merged ICDAS index. Codes 01 and 02 will be combined as “initial caries” because the 3D models cannot be dried, and codes 05 and 06 will be combined as “extensive caries” as discriminating between these latter categories is not of interest for this study (Table 1). These merged ICDAS categories still provide sufficient information about caries depth to support clinical decision-making [8,9,34].

**Table 1 table1:** Caries classification criteria for on-screen assessment of 3D models obtained with TRIOS intraoral scanners.

Caries extent	Merged ICDAS index: on-screen assessment—color		Merged modified ICDAS index: on-screen assessment—fluorescence	
Sound (ICDAS 0)	Sound tooth surfaces which show no evidence of visible caries	[figure not shown]	Sound surfaces (yellow-green fluorescence) with no visible fluorescence change (no red fluorescence)	[figure not shown]
Initial (ICDAS 1-2)	First or distinct visual changes in enamel seen as carious opacity or visible discoloration (white spot lesion and brown carious discoloration) not consistent with clinical appearance of sound enamel and which show no evidence of surface break down or underlying dentine shadowing	[figure not shown]	First or distinct visual changes in enamel seen with orange-red fluorescence and altered green fluorescence not consistent with the appearance of sound enamel and which show no evidence of surface breakdown or underlying red fluorescence from dentine	[figure not shown]
Moderate (ICDAS 3)	A white or brown spot lesion with localized microcavitation of enamel without visible dentine exposure	[figure not shown]	Lesion with localized enamel breakdown with a distinct fluorescence change (usually intense red and reduced green), without visible dentine exposure. Usually, poorly delineated fluorescence change is seen	[figure not shown]
Moderate (ICDAS 4)	Obviously discolored dentine or dark shadow visible through apparently intact or microcavitated enamel, which has originated on the surface being evaluated	[figure not shown]	Lesion with or without enamel breakdown and poorly delineated distinct fluorescence change (intense red fluorescence and significantly reduced green fluorescence which appears almost black), deriving from dentine	[figure not shown]
Extensive (ICDAS 5-6)	A distinct cavity in opaque or discolored enamel with visible dentine	[figure not shown]	Distinct cavity with visible fluorescence changes and exposed dentine	[figure not shown]

3D models will then be viewed with the addition of fluorescence texture and dental caries will be recorded using a merged ICDAS index previously described by Ferreira Zandoná et al [35], where each scoring criteria has been modified to incorporate fluorescence features (Table 1). This index enables a consistent approach to classifying carious lesions using fluorescence and has been previously validated for the on-screen assessment of 3D models [19]. If multiple lesions are present on the same tooth’s surface, the caries classification will be the more severe of the 2 clinical presentations, per VE protocol. Data will be recorded using REDCap.

A total of 4 examiners will undertake on-screen assessment. Before commencing on-screen assessment, all examiners will undergo a 2-hour training workshop followed by calibration exercises. Training will focus on applying a merged and modified ICDAS criteria to a data set of 3D models with fluorescence. A dentist and expert in using modified ICDAS to interpret 3D models (SM) will facilitate training. To establish interrater agreement, each examiner will independently undertake an on-screen assessment of a training-calibration data set of 200 examination sites. This data set includes carious lesions and sound surfaces which have been validated histologically as part of a previous study [16,20]. Examiners will repeat this calibration exercise 2 weeks after the initial assessment to establish an intrarater agreement. Examiners will repeat the calibration process until the agreement exceeds κ_w_>0.7.

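### The fluorescence codes in Table 1 leave a non-carious enamel defect without a clear code, and the planned per-person defect variable cannot isolate the surfaces affected

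*Protocol article*

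**What the plan says.** All references are to the protocol article.

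- **VE Protocol.** Two records were made per surface. For caries: "Dental caries experience was recorded for each tooth surface using the 2-digit ICDAS criteria". For defects: "Enamel defects were recorded using a modified MIH index describing each surface’s clinical presentation and the extent of the defect". Examiners were trained in both indices.
- **On-Screen Assessment, Table 1.** The table holds "Caries classification criteria for on-screen assessment of 3D models obtained with TRIOS intraoral scanners". Color code 0 reads "Sound tooth surfaces which show no evidence of visible caries", and the color initial code speaks of opacity and brown discoloration that are carious. Fluorescence code 0 reads "Sound surfaces (yellow-green fluorescence) with no visible fluorescence change (no red fluorescence"). The fluorescence initial code asks for "orange-red fluorescence and altered green fluorescence not consistent with the appearance of sound enamel" and does not say that the change must be carious.
- **On-Screen Assessment, training.** "Training will focus on applying a merged and modified ICDAS criteria to a data set of 3D models with fluorescence". The calibration set is described as carious lesions and sound surfaces. Enamel defects are not mentioned.
- **Tooth Surface Exclusion Criteria.** An enamel defect excludes a surface from automated scoring but not from on-screen assessment.
- **Outcome Measures.** The main binary threshold is sound against everything from initial caries upward.
- **Aims and Objectives; Statistical Analysis.** The third objective includes the effect of enamel defects on agreement. It is addressed by a method-by-defect interaction in the surface-level models, with the defect variable set once per person. No defect term is given for the Bland-Altman or intraclass correlation analyses of lesion counts.

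**The concern.** The main threshold lies between the sound and initial codes, so any surface whose code is unclear at that boundary feeds directly into the agreement estimates. At VE a non-carious defect had its own place on a second index. In the color reading it can be coded sound, because code 0 turns on whether caries is visible. In the fluorescence reading, code 0 turns on whether fluorescence has changed at all, and nothing separates a carious change from a non-carious one.

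If examiners resolve the ambiguity toward initial caries, fluorescence will appear to detect more lesions than VE and than color on those surfaces. If they resolve it differently from one another, interrater reliability under fluorescence also suffers. The comparison of the two on-screen methods, part of the first objective, is exposed as much as the comparison with VE. An interaction found under the third objective could not be attributed to defect surfaces, because the variable flags the whole child.

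**Working it through.** The article gives no figure to reproduce: it states no defect prevalence, caries prevalence or expected agreement. The check is a reading of the rules, followed by an illustration on assumed inputs.

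**1. The codes applied to a non-carious defect surface**

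| Appearance | Color column | Fluorescence column |
|---|---|---|
| No fluorescence change | Sound | Sound |
| Altered green, no red | Sound | Unclear: fails the no-change wording of code 0, meets its no-red gloss; the initial code asks for orange-red as well as altered green |
| Red present | Sound | Not sound; initial is the nearest code |

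Only the last two rows matter. The article does not say how often either occurs.

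**2. Illustration of the effect on agreement**

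Assume perfect agreement except on VE-sound defect surfaces. Let p be the share of surfaces positive at VE, d the share with a non-carious defect, and s the share of those coded initial under fluorescence (all assumed). Then x = d × s, observed agreement is 1 − x, the fluorescence-positive share is q = p + x, chance agreement is pe = pq + (1 − p)(1 − q), and kappa = (1 − x − pe)/(1 − pe).

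Worked case, p = 0.05, d = 0.02, s = 1: q = 0.07; pe = 0.0035 + 0.95 × 0.93 = 0.887; kappa = (0.98 − 0.887)/0.113 = 0.823.

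| p | d = 1%, s = 1 | d = 2%, s = 1 | d = 5%, s = 1 | d = 5%, s = 0.5 | s = 0 |
|---|---|---|---|---|---|
| 3% | 0.852 | 0.740 | 0.525 | 0.694 | 1.000 |
| 5% | 0.904 | 0.823 | 0.643 | 0.787 | 1.000 |
| 10% | 0.947 | 0.898 | 0.773 | 0.875 | 1.000 |

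Observed agreement stays at 0.95 or above throughout. Kappa is not the plan's measure; its surface-level measure is the method coefficient of a logistic model. The matching marginal odds ratio, before clustering, is [q/(1 − q)]/[p/(1 − p)]. At p = 0.05 and s = 1 it is 1.21 for d = 1%, (0.07/0.93)/(0.05/0.95) = 1.43 for d = 2%, and 2.11 for d = 5%.

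**3. Illustration for lesion counts**

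The Results section gives 213 eligible children. Assume 88 surfaces each (18,744) and 3% VE-positive (562).

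- Central: 213 × 0.15 of children × 4 defect surfaces × 0.5 coded initial = 64 added positives (11.4% of 562).
- Low: 213 × 0.10 × 2 × 0.25 = 10.7 (1.9%).
- High: 213 × 0.20 × 6 × 0.75 = 192 (34%).

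The central case adds 0.15 × 4 × 0.5 = 0.30 lesions per child on average, but 4 × 0.5 = 2 in each affected child.

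**4. What the per-person variable can see**

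On the same assumptions, a child flagged as having defects has 4 affected surfaces out of 88, a 22-fold dilution (88/4). A miscoding rate of 0.5 on defect surfaces becomes 4 × 0.5/88 = 2.3% averaged over all of that child's surfaces. The term pools affected and unaffected surfaces and cannot separate them.

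**The case against.** The strongest case on the other side has four parts.

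- **The wording does not force a caries code.** A reader might infer that a defect coded sound at VE has no sound code on-screen, so that disagreement follows by rule. Table 1 does not support this. Color code 0 admits a non-carious defect. Under fluorescence, altered green without red meets the gloss on code 0 and does not meet the wording of the initial code. The Introduction attributes red fluorescence to bacteria associated with caries, so the red criterion may help to separate the two. This stands, and it limits the point to an ambiguity under fluorescence.
- **Key premises are not in the document.** It never says that a defect visibly changes fluorescence on these models; the automated-scoring exclusion only hints at it. That VE gave such surfaces caries code 0 is a reasonable inference from the two-index design, but it is not stated. This stands, and it is why no size can be claimed.
- **Examiners have more context, and the article is condensed.** They see color and geometry before fluorescence, and coding conventions may sit in procedures not shown. This stands in part. The absence of an on-screen defect field or defect training is not itself an error, but Table 1 prints its criteria, and its two columns treat non-carious change differently.
- **Defects are already an objective.** True, and disagreement on defect surfaces is something the study means to measure. The planned person-level variable is nevertheless a poor instrument for it when a surface-level record exists, and the lesion-count analyses have nothing equivalent.

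**Conclusion.** The point holds as an ambiguity in the fluorescence column, combined with planned analyses that cannot locate its effect. It can produce VE-versus-fluorescence and color-versus-fluorescence disagreement at the initial threshold.

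The size is unknown. The kappa values of 0.525 to 0.947 in the full-miscoding columns, and the 1.9% to 34% added positives, rest wholly on assumed prevalences and miscoding rates. If no defect shows a scoreable fluorescence change, the effect is nil. The document does not support saying that disagreement is built in, or that the color reading is affected. The case for acting is that the question can be answered from data already held.

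**What to change.** 1. **Leave the index and the second-round scoring rules unchanged.** The Results section says on-screen assessment has commenced. The second round replicates the first, and intrarater reliability is to be reported. A new code or wording between rounds would mix a rule change into those estimates.
2. **Report initial-threshold agreement with and without VE-flagged defect surfaces**, for color and for fluorescence, in both the surface-level models and the lesion-count analyses. Use the surface-level defect record from VE.
3. **Replace the per-person defect variable with the surface-level one** in the method-by-defect interaction of the on-screen models. In the VE-versus-automated model it would have no variation, because defect surfaces are already excluded there.
4. **Only if scoring had not started**, also state in Table 1 and in the training how a non-carious defect is coded for caries under fluorescence.

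The cost is a little more analysis work and slightly fewer surfaces in the restricted runs, including any defect surfaces that also carry caries. The with-and-without comparison shows how much of the disagreement lies on flagged surfaces. It does not by itself show whether the cause is the coding rule or a true limit of the images, and it relies on VE having found the defects.
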